#### Health providers

Health providers will complete a demographic survey (age, gender, profession, years of experience in profession, and whether they have completed elder abuse training prior to the trial). They will also complete the adapted Knowledge and Management of Abuse (KAMA) [27] (primary outcome) adapted for an Australian subacute care setting, the Australian adaptation of the Caregiver Scenario Questionnaire (CSQ) [28, 29], and Carolina Opinions on Care of Older Adults (COCOA) survey [30] (secondary outcomes) via online survey in REDCap.

#### Older people

Older people will complete a demographic survey (age, gender, education, postcode, country of birth, language/s spoken, English language skills, First Nations status, reason for admission and underlying health risk factors for elder abuse (e.g. dementia, mobility), the Adult Social Care Outcomes Toolkit (ASCOT) [31] (primary outcome), the Short Form Survey-12 (SF-12v2) [32], and an adapted Resource Utilisation in Dementia lite (a-RUD-lite) (secondary outcomes) via online/paper/telephone survey. Site champions will support older people where required and record the older person’s length of admission once discharged.

**Table 1 Tab1:** Procedure timeline

**Procedures**	**Assessment/procedure**	**Screening**	**Baseline**	**4-month follow-up**	**9-month follow-up**
	**Health providers**				
	** Informed consent**	**x**			
	** Demographic Information**		**x**		
	** a-KAMA questionnaire**		**x**	**x**	**x**
	** CSQ**		**x**	**x**	**x**
	** COCOA questionnaire**		**x**	**x**	**x**
	**Older adults**				
	** Informed consent**	**x**			
	** Demographic Information**		**x**		
	** ASCOT questionnaire**		**x**	**x**	**x**
	** SF-12v2 questionnaire**		**x**	**x**	**x**
	** a-RUD-lite questionnaire**		**x**	**x**	**x**
	** Has patient attended another hospital in trial during study period**		**x**	**x**	**x**
	**Administrative/site data**	**9 months prior to Baseline**	**Baseline**	**Baseline to 4 months**	**4-months to 9 months**
	** Elder abuse cases**	**x**	**x**	**x**	**x**
	** Elder abuse referrals**	**x**	**x**	**x**	**x**
	** Nature of referral**	**x**	**x**	**x**	**x**
	** Number of eligible clinicians (total and by profession)**		**x**	**x**	
	** Number of clinicians who have completed the training (total and by profession)**		**x**	**x**	
	** Number of times the screening tool was administered/not administered**		**x**	**x**	**x**

#### Process evaluation

We will conduct a multi-method process evaluation on how the intervention works in practice. Training completion rates will be monitored using the NARI Learning Management System. In addition to monitoring uptake of the screening tool, a researcher will visit each intervention site for 2–3 days approximately 3 months after implementation of the screening tool. We will observe how the screening and referrals are conducted and interview site champions and 20–25 health providers across the sites. This evaluation will mobilise WHO guidance for scaling up health service innovations [33] as we seek to understand the following: intervention uptake, potential facilitators/barriers, and solutions; whether the essential features of the intervention are being adhered to in practice (and if not, what remedial action can or should be taken); and whether the intervention improved elder abuse detection and response and impacted practice and provider satisfaction.

### Sample size

As health providers are not anticipated to be systemically different based on location (clusters), we have not accounted for ICC for health providers; therefore, we calculated that 60 health providers would be sufficient to detect a medium effect (Cohen’s *d* of 0.5) on the KAMA at a power of 80% and a significance level of 1%. This difference is similar to that reported in our previous research, and the sample size calculation uses a standard deviation of 4.8 as previously reported [34]. We calculated that we need 10 clusters (5 intervention, 5 control) with 40 older people in each cluster to detect a medium effect on the ASCOT at a power of 80% and a significance level of 5%. As responses to elder abuse vary across jurisdictions, an ICC of 0.1 is assumed for older people with the standard deviation of 0.2 reported by others [35], calculated using the Shiny Calculator for Sample size for Cluster Randomised Trials [36]. Assuming 53% refusal rate to participate/unable to consent as observed in our group’s prior work in the UK [37, 38], the total sample size is 92 health providers and 612 older people (~ 60 older people/site).

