**Methods:**

This is a single-blinded, pragmatic, cluster randomised controlled trial. Ten subacute hospital sites (i.e. clusters) across Australia will be allocated 1:1, stratified by state to a multi-component intervention comprising a training programme for health providers, implementation of a screening tool and use of site champions, or no additional training or support. Outcomes will be collected at baseline, 4 and 9 months. Our co-primary outcomes are change in health providers’ knowledge of responding to elder abuse and older people’s sense of safety and quality of life. We will include all inpatients at participating sites, aged 65 + (or aged 50 + if Aboriginal or Torres Strait Islander), who are able to provide informed consent and all unit staff who provide direct care to older people; a sample size of at least 92 health providers and 612 older people will provide sufficient power for primary analyses.

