### Analysis

#### Primary and secondary RCT outcomes

The primary analysis will be performed according to intention to treat, including all clusters and participants in the allocated groups. Between-group difference for both primary outcomes (health provider and older people) will be analysed using mixed effects regression models with a fixed effect for the intervention group and random effect for participants to account for repeated measures. Cluster site will also be added as a random effect. Due to the likelihood of differences across sites, a number of baseline covariates will be controlled for in the analyses (as listed in Table 2).

**Table 2 Tab2:** List of covariates to be used in analysis and source

	*Health provider outcomes*	*Older adult outcomes*
*Self-reported*	Profession, age, gender, years in the role	Age, sex, ethnicity, location, educational and economic attainments, country of birth, English proficiency, reason for subacute stay, and admission to any other hospital in the trial
*Reported by site champion based on data routinely collected by hospitals, or case records*	General characteristics of the site (size of workplace, location, subacute services offered), average characteristics of older patient cohorts admitted to the participating wards (age, gender, country of birth, English proficiency, reason for subacute stay), and elder abuse cases (number of suspected elder abuse cases p/month, number, and types of referral) to enable the evaluation and statistical control of differences between sites	Length of hospital admission, length of admission on participating ward; number of eligible clinicians (total and by profession), and number of clinicians who have completed the training (total and by profession) to provide a measure of ‘dose’

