We will similarly analyse secondary outcomes. Continuous outcomes will be analysed using mixed effects linear regression models and adjustment for baseline values. Statistics will be reported with their respective 95% confidence intervals and *P* values. Per-protocol analyses will also be performed, omitting participants with predefined protocol deviations (e.g. allocated intervention not received, violated inclusion/exclusion criteria). The trial results will be reported in line with the CONSORT extension for cluster trials. As this is a low-risk, non-medical intervention, no interim analyses will be conducted, and no stopping guidelines were developed for ceasing the trial early. Similarly, as adverse events reporting is only required for medical interventions, we do not report these.

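### The health-provider sample size of 60 (92 after inflation) does not follow from its stated inputs: d = 0.5 at 1% significance with 80% power needs about 192 providers two-sided, or about 164 one-sided

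*Protocol article*

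**What the plan says.** The Sample size section of the protocol article states that "we calculated that 60 health providers would be sufficient to detect a medium effect", defined as a Cohen's d of 0.5 on the KAMA, "at a power of 80% and a significance level of 1" per cent. The SD is 4.8. On clustering it says "we have not accounted for ICC for health providers", on the ground that providers are not expected to differ by location. After a 53% allowance for refusal or inability to consent, the total becomes 92. The abstract concludes that "a sample size of at least 92 health providers and 612 older people will provide sufficient power for primary analyses".

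Other sections fix the comparison. Aims and hypotheses compares provider knowledge in the intervention arm with the control arm at 4 months. The abstract gives 1:1 allocation of ten sites. The section on primary and secondary RCT outcomes specifies a mixed model with random effects for participant and site, and adjustment for baseline values. It also says: "Due to the likelihood of differences across sites, a number of baseline covariates will be controlled for in the analyses". Table 2 lists site characteristics among the covariates for provider outcomes.

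**The concern.** The section gives the effect size, SD, power, significance level and clustering assumption, so its figure can be checked, and 60 looks far too small for a two-arm comparison at 1%. The KAMA is a co-primary outcome. If its power is well below the stated 80%, a non-significant provider result could be read as evidence that the training does not improve knowledge, when the trial was unlikely to detect the planned effect.

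The zero ICC pushes the same way. Sites are the randomised units, and the site champion and training uptake operate at site level. The analysis model allows for site variation that the sample size rules out.

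**Working it through.** **Inputs.** From Sample size: d = 0.5, SD 4.8 (so 0.5 × 4.8 = 2.4 points), power 80%, significance 1%, no ICC. From the abstract: 1:1 allocation. From Aims and hypotheses: a between-arm contrast at 4 months. Sidedness is not stated, so both are tried. The 60 is read as a trial total, because 60 × 1.53 = 91.8, which rounds to the stated total of 92.

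**Attempt to reproduce 60.** For two arms, n per arm = 2(z₁₋α/₂ + z₀.₈)²/d².

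- Two-sided 1%: 2(2.576 + 0.842)²/0.25 = 93.4. The t-test solution is 95.1, so 96 per arm and 192 in total (95 per arm gives 79.95% power).
- One-sided 1%: 2(2.326 + 0.842)²/0.25 = 80.3. The t-test solution is 81.7, so 82 per arm and 164 in total.
- Two-sided 5%: t-test solution 63.8, so 64 per arm and 128 in total.
- 60 read as per arm (120 in total): 55% power at two-sided 1%.
- Single-group paired test, two-sided 1%: t-test solution 50.1, so 51. This is not the trial's contrast.

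None of these gives 60.

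**What 60 and 92 deliver** (unadjusted two-sample t-test, two-sided 1%, no ICC).

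| Total providers | Power at d = 0.5 | Detectable difference at 80% power |
|---|---|---|
| 60 | 24.4% | 0.909 SD × 4.8 = 4.4 points |
| 92 | 41.2% | 0.726 SD × 4.8 = 3.5 points |

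At one-sided 1% the powers are 33% and 51%. At two-sided 5% they are 48% and 66%.

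**Allowing for baseline adjustment.** With baseline-to-follow-up correlation r, the residual variance is multiplied by 1 − r². The correlations below are assumptions, since the document gives none.

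| Assumed r | Power, 60 | Power, 92 |
|---|---|---|
| 0.5 | 34% | 56% |
| 0.7 | 52% | 76% |

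To reach 80%, the normal formula requires 1 − r² = 30/93.4 for 60, so r ≈ 0.82, and 1 − r² = 46/93.4 for 92, so r ≈ 0.71. The t-test needs slightly more.

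**Allowing for clustering.** With 92 providers in 10 sites (9.2 per site) the design effect is 1 + 8.2 × ICC. The ICC values are assumptions.

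| Assumed ICC | Design effect | Unadjusted power, 92 at two-sided 1% (normal) |
|---|---|---|
| 0 | 1 | 43% |
| 0.01 | 1.082 | 39% |
| 0.05 | 1.41 | 29% |

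A t reference with 8 degrees of freedom (10 sites less 2 arms) gives 23% at ICC 0.01 and 17% at 0.05.

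**What 92 represents.** The powers for 92 treat all 92 as analysed. If 92 were the number approached and 53% declined, 92 × 0.47 ≈ 43 would remain, with unadjusted power of about 16% (18% by normal approximation).

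**The case against.** The strongest reply is that the planned analysis is not a plain t-test. It is a repeated-measures mixed model with baseline adjustment, so its power exceeds 24% or 41%. That stands, and those two figures describe an unadjusted test only. A reader might infer that they are the trial's true power, but the documents do not support this. Nor do they support 80%, because no correlation is stated or credited and the values required are high.

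A second reply is that some standard calculation may lie behind 60. A group-by-time calculation with a medium f of 0.25, two groups, three assessments, 1% significance and 80% power gives 62 at an assumed correlation of 0.2 and 56 at 0.3. So it cannot be said that no standard routine lands near 60. But that f is a different quantity from a between-arm d of 0.5 at 4 months, which is what the text claims to detect.

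Third, 92 is a minimum, and the abstract intends to include all unit staff giving direct care. More providers may enrol, but the claim under review is that 92 suffices.

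Three further inferences are tempting and should not be drawn:

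- The site random effect is not justified by likely site differences. The article gives that reason for the covariates, and the random effect is stated without one. The tension with a zero ICC remains.
- "Statistics will be reported with their respective 95% confidence intervals" does not contradict sizing at 1%. It is general reporting language, and the test level may be set in an analysis plan that is not shown.
- The size of the clustering loss is not established, because the documents give no KAMA ICC. Only its direction is.

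**Conclusion.** The stated provider sample size is wrong as written. The inputs given require about 192 providers (two-sided) or about 164 (one-sided), roughly three times the stated 60 and about twice the inflated 92. This rests on reading 60 as a total and the contrast as between arms at 4 months, and the text supports both.

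Actual power depends on a correlation and an ICC that the article does not give, so no single figure can be assigned. Baseline adjustment moves it up and any non-zero ICC moves it down. The abstract's assurance that 92 is sufficient is unsupported unless an unstated correlation of about 0.71 or more is credited, and even then only with no clustering.

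**What to change.** In the Sample size section and the abstract, replace the claim that 60 (92) providers give 80% power at 1% with the re-derived power and detectable KAMA difference for the number expected to be analysed. State the sidedness, any baseline correlation credited and its source, and results over a range of non-zero ICCs across 10 sites (for example 0.01 to 0.05, labelled as an assumption). Remove the justification for a zero provider ICC. If a different calculation produced 60, give its contrast and inputs. No change to the reported confidence intervals is needed on this account.

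Restating the power needs only a wording change. The downside is that the stated power becomes less favourable. If the sponsor prefers to keep 80% power, the provider target must rise or the credited correlation must be justified, which is more than a wording change.

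### Sixty health providers give about 24% power for the co-primary KAMA on the stated inputs, not 80%; about 190 would be needed

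*Protocol article*

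**What the plan says.** The Sample size section of the protocol article gives a full set of inputs for the health-provider outcome. It says "we calculated that 60 health providers would be sufficient to detect a medium effect", defined as Cohen's d of 0.5, "on the KAMA at a power of 80% and a significance level of 1"%. It adds that "the sample size calculation uses a standard deviation of 4.8 as previously reported" and that "we have not accounted for ICC for health providers". The number is then inflated: "Assuming 53% refusal rate to participate/unable to consent", "the total sample size is 92 health providers and 612 older people".

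The abstract carries the result forward: "a sample size of at least 92 health providers and 612 older people will provide sufficient power for primary analyses".

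KAMA is one of two co-primary outcomes. Under Aims and hypotheses, its test is a comparison between arms at 4 months. The Sample size section does not give the sidedness of the test, a baseline to follow-up correlation, or any gain from repeated measures for the KAMA calculation.

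**The concern.** A two-group comparison at d = 0.5 with 80% power takes about 64 per arm at the conventional two-sided 5% level, and more at 1%. A total of 60 at the stricter level is too small on its face.

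This is separate from three other questions: ignoring the ICC for providers, the way refusal is allowed for, and a 1% level alongside 95% confidence intervals. The mismatch remains with ICC = 0, no refusal and a 1% test.

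At stake is the stated power of a co-primary outcome. If the trial analyses about the planned number, a null KAMA result could be read as evidence against the training when the trial was unlikely to detect the effect it was designed for.

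**Working it through.** **Inputs.** From the Sample size section: d = 0.5, SD 4.8 (so a difference of 0.5 × 4.8 = 2.4 points), power 80%, level 1%, no ICC, 60 providers before inflation and 92 after. From the abstract: 1:1 allocation (of sites), so equal arms of providers are assumed. From Aims and hypotheses: a between-arm contrast at 4 months. Assumption: two-sided test, because sidedness is not stated.

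**Is 60 a total or per arm?** The inflation is 60 × 1.53 = 91.8, rounded to 92, which the section calls a total. The older-people figure is built the same way: 10 clusters × 40 = 400, and 400 × 1.53 = 612. So 60 is the total, or 30 per arm.

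**Attempt to reproduce 60.** Normal approximation:

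n per arm = 2(z₀.₉₉₅ + z₀.₈₀)² / d² = 2(2.576 + 0.842)² / 0.25 = 93.4, so 94 per arm and 188 in total.

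The noncentral t gives 95.1 per arm, so about 190 in total (192 if each arm is rounded up). The stated 60 is not reproduced.

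**Power at the stated numbers** (two-sided 1%, d = 0.5, ICC 0, noncentral t). The noncentrality is d√(n/2); for 30 per arm it is 0.5 × √15 = 1.94.

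| Total analysed | Per arm | Power |
|---|---|---|
| 60 | 30 | 24% |
| 92 | 46 | 41% |
| 120 (60 read as per arm) | 60 | 55% |
| 190 | 95 | 80% |

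**Effect detectable with 80% power.** With 60: d = 0.91, or 0.91 × 4.8 = 4.4 points. With 92: d = 0.73, or 0.73 × 4.8 = 3.5 points. The planned difference is 2.4 points.

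**Other readings without baseline adjustment.**

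| Reading | Total needed for 80% | Power with 60 in total |
|---|---|---|
| One-sided 1% | 164 | 33% |
| Two-sided 5% | 128 | 48% |
| One-sided 5% | 102 | 61% |
| Single-group pre-post test, two-sided 1%, d = 0.5 on the change | 51 | not a between-arm test |

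Reading 60 as per arm at two-sided 5% comes closest, at 78%, but contradicts both the stated 1% level and the total of 92.

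**With adjustment for baseline KAMA.** Replace d by d/√(1 − r²), where r is the baseline to 4-month correlation. The article gives no r, so a range is shown (two-sided 1%, ICC 0).

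| r | Total needed for 80% | Power with 60 | Power with 92 |
|---|---|---|---|
| 0.5 | 144 | 34% | 56% |
| 0.7 | 99 | 52% | 76% |
| 0.83 | 62 | 79% | 95% |
| 0.84 | 59 | 81% | 96% |

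Sixty reaches 80% only at r of about 0.83 to 0.84; 92, if all are analysed, reaches it at about 0.73.

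**The case against.** The best counter-argument is that 24% describes an unadjusted t test, while the Analysis section plans mixed models with repeated measures, baseline adjustment and covariates. Baseline adjustment does raise power, and at a high enough correlation it makes 60 adequate. So the 24% is conditional on no baseline gain, and 92 analysed providers would have better than even power at r = 0.5.

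The threshold also depends on the model. The Analysis section names a group effect without a time interaction. If that effect averages the 4- and 9-month scores with baseline adjustment (equal correlation r between all visits), the variance factor is (1 + r)/2 − r². Then 60 reaches 80% at r of about 0.76, and 92 at about 0.55. That averaged effect is not the 4-month hypothesis in Aims and hypotheses, so it is a caveat and not a reproduction of the figure.

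Two further points are fair. The abstract sets 92 as a minimum, so more providers may be recruited. The article also condenses a fuller protocol that may give more detail.

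None of this makes the printed statement correct. The section lists its inputs and a result, names neither a correlation nor an adjusted method, and the result does not follow. A correlation of about 0.83 or more would have to be shown, not assumed.

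**Conclusion.** The concern holds. On the stated inputs, with a two-sided test, equal arms and independent providers, 60 analysed providers give about 24% power for d = 0.5, against the stated 80%; about 190 are needed. A true medium effect would be missed about three times in four with 60. Without baseline adjustment it would be missed more often than not even if all 92 were analysed.

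A one-sided 1% test raises power at 60 only to 33%. Only an unstated baseline correlation of about 0.83 to 0.84 would justify 60 for the 4-month contrast. Any positive ICC among providers lowers power further: with 6 per site and the normal approximation, it falls from 26% at ICC 0 to about 20% at ICC 0.05 and 16% at 0.10. As written, the abstract's statement of sufficient power is unsupported for KAMA.

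**What to change.** Correct the Sample size section and the abstract.

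- State the test, its sidedness and whether baseline adjustment was assumed. If it was, give the correlation and its source, and recompute for the between-arm difference at 4 months.
- If no such correlation was used, state that d = 0.5 with 80% power at two-sided 1% needs about 190 analysed providers. State also that 60 and 92 analysed give about 24% and 41% power, with detectable effects of d = 0.91 and 0.73 (4.4 and 3.5 points).
- Remove the claim of sufficient power for KAMA from the abstract until the recomputation supports it.

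The cost is wording in the protocol and the analysis plan, and a less favourable stated power. The correction itself requires no extra enrolment. The article reports that recruitment has already begun, so the record should be corrected before results are known.

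### The KAMA co-primary is sized at a 1% significance level, but the analysis section specifies only 95% confidence intervals and P values, so the level at which KAMA will be judged is unresolved

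*Protocol article*

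**What the plan says.** The protocol article names two co-primaries: KAMA in health providers and ASCOT in older people. The Aims and hypotheses section places both at 4 months.

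The Sample size section gives them different significance levels. Sixty providers are said to be enough for a Cohen's d of 0.5 "on the KAMA at a power of 80% and a significance level of 1"%, while the older-person sample is meant to "detect a medium effect on the ASCOT at a power of 80% and a significance level of 5"%. No reason is given for the difference, and sidedness is not stated. For KAMA, "the sample size calculation uses a standard deviation of 4.8 as previously reported" and "we have not accounted for ICC for health providers". The total of 92 providers follows after an allowance for refusal.

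The Analysis section (Primary and secondary RCT outcomes) applies mixed models to both primary outcomes, handles secondary outcomes similarly, and then says: "Statistics will be reported with their respective 95% confidence intervals and *P* values". The 1% level is not carried forward, and no different interval is set for KAMA.

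**The concern.** A 95% interval corresponds to a two-sided 5% test, and a two-sided 1% test corresponds to a 99% interval. The interval planned for KAMA is therefore not the one that matches the level at which KAMA was sized.

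The practical risk lies in the band 0.01 < P < 0.05. There, a reader of the results would see a 95% interval excluding zero on a co-primary outcome, while the only KAMA level that the article states would not be met. If nothing else fixes the level, it could be settled once the result is known. The sample size would normally show which level was meant, so the check below asks whether it does.

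**Working it through.** **Inputs.** From the Sample size section: d = 0.5 (2.4 points at SD 4.8), power 80%, level 1% for KAMA, no intracluster correlation for providers, 60 providers before and 92 after inflation. From the abstract: 1:1 allocation by site. Two-sided testing is assumed unless stated otherwise.

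**1. Does the sample size identify the level?** For two arms, n per arm = 2(z₁₋α/₂ + z₀.₈₀)²/d².

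- Two-sided 1%: 2(2.576 + 0.842)²/0.25 gives 94 per arm, 188 in total (t-based: 96 per arm, 192).
- Two-sided 5%: 2(1.960 + 0.842)²/0.25 gives 63 per arm, 126 in total (t-based: 64 per arm, 128).
- One-sided 1% gives 162 in total and one-sided 5% gives 100 (normal approximation).
- A one-group or paired t test gives 51 at two-sided 1% and 34 at two-sided 5%.

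None of these is 60. The 92 is 60 × 1.53 = 91.8, rounded up, and is called a total, so 60 also reads as a total. If 60 were per arm, power would be about 56% at 1% and 78% at 5% (normal approximation).

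Baseline adjustment could change this. With ANCOVA, the total at two-sided 1% is about 4(1 − r²)(2.576 + 0.842)²/0.25. Setting it to 60 gives 1 − r² = 60/186.9 = 0.321, so r ≈ 0.82. At 5% the same step gives 1 − r² = 60/125.6 = 0.478, so r ≈ 0.72. The article states no correlation, and each level has an r that fits, so 60 does not identify the level.

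**2. Power at each level** (unadjusted two-sample t test, d = 0.5, no clustering, two-sided):

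| Providers analysed (total) | Power at 1% | Power at 5% | Chance that 0.01 < P < 0.05 |
|---|---|---|---|
| 60 | 24% | 48% | 23% |
| 92 | 41% | 66% | 25% |

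The last column is the difference between the two powers (0.478 − 0.244 and 0.660 − 0.412). The 92 row is a best case, because 92 is the figure after allowing for refusal.

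**3. The same band if the design power were real.** With 80% power at two-sided 1%, the expected z is 2.576 + 0.842 = 3.417. Power at 5% is then Φ(3.417 − 1.960) = 0.928, and the band holds 0.928 − 0.800 = 0.128, about 13%. Under the null it holds 0.05 − 0.01 = 4%.

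**4. Sidedness.** The hypotheses are directional. If the 1% were one-sided, it would equal two-sided 2% and match a 98% interval. The mismatch with 95% would narrow but remain.

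**The case against.** The strongest reply is that the Analysis sentence is a reporting convention. It sets no threshold and does not say that an interval excluding zero counts as success. Reporting a 95% interval with a P value is compatible with judging KAMA at 1%, because the P value allows that judgement. The decision threshold, sidedness and any multiplicity rule may sit in an analysis plan or full protocol that is not shown, and sizing one outcome at a stricter level is not in itself an error.

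All of this stands. A reader might infer that a KAMA result with P between 0.01 and 0.05 is declared positive by one section and negative by the other, or that the analysis as written has a 5% false-positive rate for KAMA. The article supports neither inference. Both need the added assumption that a 95% interval excluding zero is the success criterion. Nor can it be said that no calculation yields 60, because a high baseline correlation would.

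The reply does not remove the mismatch itself. The article chose to state a separate level for one co-primary and then specified an interval that does not correspond to it. That is a feature of the published text, not a detail left out of it.

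**Conclusion.** The point holds as an unresolved mismatch between the level used to size KAMA (1%) and the level implied by the planned intervals (5%). Its size is the probability of a result on which the two diverge: about 13% if power were truly 80% at 1%, and about 23% to 25% with 60 to 92 providers analysed. These figures assume a true effect of d = 0.5, a two-sided unadjusted t test and no clustering. They are the chance that P falls in the band, not the chance that two documented rules conflict.

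The stated sample size does not settle which level was meant, and settling the level does not repair the power. On the unadjusted calculation, 60 or 92 providers fall short of 80% at either level. This should be corrected, but it is mainly a clarification of the decision level. The shortfall in provider numbers is a larger, separate matter.

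**What to change.** Make one of two changes before outcome data are unblinded, since the Trial status section says that recruitment has begun:

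- **Keep 1%.** State in the Analysis section that KAMA at 4 months is tested at 1%, give the sidedness, and report the matching interval (99% if two-sided). A 95% interval may be added as a descriptive extra. ASCOT keeps its 5% level and 95% interval.
- **Use 5%.** Correct the level for KAMA in the Sample size section to 5% and leave the 95% interval as it is.

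In either case, restate the KAMA power at the chosen level, with the number analysed. If baseline adjustment is relied on, state the assumed correlation and its source.

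The cost is about two sentences plus the restated power, and a registry update; this correction requires no further participants. The downside should be stated openly. Keeping 1% makes the KAMA criterion stricter and clearly lowers its power (24% against 48% with 60 providers, 41% against 66% with 92, unadjusted). Either choice makes the published power statement less favourable than it now is.

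### The stated inputs for the ASCOT (10 sites of 40, ICC 0.1) give about 62% power for d = 0.5, or 51% with cluster-level degrees of freedom, not 80%; a two-sided test without baseline gain cannot reach 80% at any cluster size

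*Protocol article*

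**What the plan says.** The Sample size section sets out the calculation for the older-person co-primary outcome: "we need 10 clusters (5 intervention, 5 control) with 40 older people in each cluster to detect a medium effect on the ASCOT", at 80% power and a 5% significance level. It adds that "an ICC of 0.1 is assumed for older people with the standard deviation of 0.2", and attributes the calculation to a Shiny calculator for cluster randomised trials. No target difference in ASCOT units is given, and sidedness is not stated. Nor is any baseline correlation, cluster autocorrelation or variation in cluster size.

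The word medium is given a number once in the paragraph, for the health-provider outcome: "detect a medium effect (Cohen’s *d* of 0.5) on the KAMA".

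The total is then raised to 612, about 60 per site, for refusal. The abstract concludes that "a sample size of at least 92 health providers and 612 older people will provide sufficient power for primary analyses".

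**The concern.** With only five sites per arm and an ICC of 0.1, between-site variation dominates the standard error of the ASCOT comparison. In that situation power depends mainly on the number of sites, and recruiting more people at each site adds little. A claim of 80% power for a half-SD effect from ten sites at this ICC therefore needs checking.

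The ASCOT is one of two co-primary outcomes, and the primary outcome of the economic evaluation is built from it. If the true power is between a half and two thirds, a real medium effect would be missed roughly four or five times in ten. Readers who took the stated 80% at face value would give a non-significant result more weight than it deserves.

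**Working it through.** **Inputs.** From the Sample size section: k = 5 sites per arm, m = 40 per site, ICC ρ = 0.1, SD 0.2, α = 0.05, stated power 80%. Assumed: two-sided test; d = 0.5 carried over from the KAMA sentence, which is 0.5 × 0.2 = 0.10 ASCOT units; equal cluster sizes; no loss to follow-up; no gain from baseline adjustment.

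**Step 1: effective sample size.**
- Design effect: 1 + (m − 1)ρ = 1 + 39 × 0.1 = 4.9.
- Effective n per arm: 5 × 40 / 4.9 = 40.8.

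**Step 2: power at the stated design.**
- Noncentrality: d × √(n_eff/2) = 0.5 × √(40.8/2) = 2.26.
- Normal approximation: Φ(2.26 − 1.96) = 0.617.
- Noncentral t with 2 × 5 − 2 = 8 df: 0.510.

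The stated 80% is not reproduced; the gap is 18 to 29 percentage points.

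**Step 3: can more people per site close the gap?**
- As m grows, n_eff per arm tends to k/ρ = 5/0.1 = 50.
- Required n per arm for 80% power is 2(1.96 + 0.84)²/0.5² ≈ 62.8.
- Since 62.8 > 50, no cluster size suffices. Equivalently, 62.8 × 0.1 = 6.28 exceeds the 5 sites per arm.

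| People per site | n_eff per arm | Power, normal | Power, t (8 df) |
|---|---|---|---|
| 40 | 40.8 | 61.7% | 51.0% |
| 61.2 (all 612 analysed) | 43.6 | 64.6% | 53.6% |
| unlimited | 50 | 70.5% | 59.3% |

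**Step 4: what would give 80% with 5 × 40 per arm?** Each row changes one input and holds the others.

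| Changed input | Normal | t (8 df) |
|---|---|---|
| Larger effect | 0.62 SD (0.124 ASCOT units) | 0.71 SD (0.142 ASCOT units) |
| Smaller ICC | 0.056 | 0.037 |
| Baseline correlation, same at individual and site level | 0.59 | 0.71 |

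The last row uses the variance factor 1 − r², which would have to fall to 0.65 (normal) or 0.50 (t).

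With all 61.2 per site analysed, the effect detectable with 80% power is 0.60 SD (normal) or 0.69 SD (t).

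**Step 5: sites needed.** At m = 40, ρ = 0.1 and d = 0.5, 80% needs 8 sites per arm by the normal approximation (81.5%) or 9 per arm by the t calculation (81.2%).

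**Step 6: a one-sided test.** At one-sided 5% the stated design has 73.0% (normal) or 66.2% (t). With unlimited cluster size the limits are 80.4% and 73.8%.

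**The case against.** The arithmetic is not in dispute. The case on the other side is about the conditions attached to it.

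- **The effect size is inferred.** The protocol gives d = 0.5 for the KAMA only, and a target of 0.62 to 0.71 SD would reproduce 80%. This stands as a condition. But 0.5 is the only value the paragraph attaches to medium, and if a larger effect was intended the paragraph fails to say so.
- **Sidedness is not stated.** The statement that no cluster size can reach 80% holds for a two-sided test, or for any test on 8 df. A one-sided normal approximation creeps to 80.4% in the limit. That does not help at 40 or 61 per site.
- **The planned analysis is not post-intervention only.** The Analysis section plans repeated-measures mixed models and adjustment for baseline values, which can raise power. This is the most substantial point, and it means that 51% is not shown to be the power of the planned model. The sample size calculation, however, credits no such gain, and the correlation needed is high at site level as well as individual level. In addition, the Recruitment section has older people enrolled only after training is complete and the screening tool is in place. Their baseline is therefore not a pre-intervention measure: it could still correlate with the outcome, but adjusting for it may also remove part of the effect.
- **State may absorb some between-site variance.** The ICC is justified by differences between jurisdictions, and randomisation is stratified by state. Any gain is unquantified, and adjusting for state would use up scarce degrees of freedom.
- **A null result would still carry some information.** The standard error is √(2/40.8) = 0.221 SD, so the 95% half-width is 0.43 SD (normal) or 2.306 × 0.221 = 0.51 SD (t). An estimate very near zero would just exclude, or sit at the edge of excluding, half an SD. A null result would therefore be weak evidence, though not worthless.

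None of these restores 80% from the inputs as written.

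**Conclusion.** The concern holds. On the inputs stated, the ASCOT comparison has about 62% power (normal) or 51% (t, 8 df) for d = 0.5, against the 80% claimed, and the enlarged total of 612 brings it only to 65% or 54%. The abstract's statement that 612 older people are sufficient is therefore wrong as written.

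The figures rest on four assumptions: medium means d = 0.5, the test is two-sided, there is no baseline gain, and ICC 0.1 is the value actually entered. The first two follow the paragraph's own definition and ordinary convention; the third reflects that no correlation is stated. The figures are also somewhat generous, because unequal site sizes and loss before 4 months are ignored.

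**What to change.** In the Sample size section:

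1. Give the ASCOT target difference as a number, in ASCOT units and SDs, with the sidedness of the test. List every input entered in the calculator. If the run used a different ICC, a baseline correlation or a larger effect, state its value and justify it.
2. If no such input was used, restate the power for 10 sites at ICC 0.1: about 51 to 54% for d = 0.5 with 8 df. Alternatively, state the difference detectable with 80% power: about 0.69 to 0.71 SD, or 0.14 ASCOT units.
3. Add sensitivity to the ICC. At 40 per site and d = 0.5, power (normal / t) is 96% / 91% at ICC 0.02, 83% / 72% at 0.05, 69% / 58% at 0.08 and 62% / 51% at 0.10.
4. Amend the abstract so that it no longer says that 612 older people give sufficient power.

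This changes wording in the protocol and the SAP and needs no extra patients. The cost is a less favourable power statement. Keeping 80% for d = 0.5 at ICC 0.1 without relying on baseline adjustment would need more sites, 8 or 9 per arm, which is a different and much larger decision.
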